#### Secondary outcomes

Change in performance-based function (walking distance in 6 min and climbing of stairs), current knee pain and during the last week (numerical rating scale), self-reported disability (Knee Osteoarthritis Outcome Score and Oxford Knee Score) as recommended by Osteoarthritis Research Society International [33, 34], need for surgery and exercise adherence (sessions, sets, reps, TUT).

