##### Exercise adherence

A large challenge regarding home-based exercise is that adherence to home-based exercise is reported to be poor [45–48], suggesting low effect of the exercise interventions. To take into account the possibility of non-adherence to the intervention (which could distort the possible conclusion that the intervention did not work), we will objectively quantify exercise adherence. Adherence to the home-based, single knee-extensor strength exercise will be assessed using a sensor (BandCizer technology) attached to the elastic exercise band used for the knee-extensor strength exercise. The sensor stores data on date, time, number of sets, repetitions, tonnage (kg × repetitions) and TUT. This elastic exercise band sensor technology has been reported to be valid [49] and reliable (ICC > 0.99) [50] for quantification of total repetition, single repetition and contraction specific TUT of an unsupervised exercise intervention.

In the present trial, patients are defined as adherent to the exercise intervention if > 75% of the prescribed exercise sessions are completed. Correspondingly, 1.5 sessions/week must be completed in group 2, three sessions/week in group 4 and 4.5 sessions/week in group 6. After the 12-week exercise period, the patients who undergo surgery are encouraged to continue exercising (same dosage) until the day of surgery. The exercise adherence during this period will also be quantified by use of the sensor. Patients deciding not to undergo surgery following the 12 weeks of exercise are encouraged to keep exercising, but exercise adherence will not be quantified. Figure 4 shows an example of objectively quantified exercise adherence via the sensor attached to the elastic exercise band. The example shows a knee-extensor strength exercise session composed of three sets with 12 repetitions in each set resulting in 36 repetitions in total for the exercise session. Number of repetitions, total TUT, mean TUT for the 36 repetition and the corresponding standard deviation can be extracted. This is also possible for single exercise sets (Fig. 5).

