10. Difference in *adherence to intervention* between groups	Group 2 > Group 4 Group 4 > Group 6 Group 2 > Group 6 We hypothesize differences between groups in adherence (%) to the training intervention (i.e., higher number of sessions per week, the lower adherence (%))	Number of sessions, sets, repetitions and time-under-tension	ANOVA^a^

^a^If data are not normally distributed the non-parametric Kruskal-Wallis test will be used

Analysis of variance: (ANOVA)

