**Fig. 7 Fig7:**
[figure not shown]
A hypothetical presentation of group changes in knee-extensor strength over the whole trial period. NB, control data are from the academic literature [11] and so are the healthy, age-matched, control data (age 66.8 years (6.5 SD)) [7]

For all outcomes (primary and secondary), mean scores with corresponding standard deviations (SD), and between-group contrasts (change scores) with corresponding 95% confidence intervals (95% CI) and *p* value, will be reported at each endpoint (t_0_, t_1_, t_2_ and t_3_) for each group (groups 2, 4 and 6) (Table 4).

**Table 4 Tab4:** Outcomes for primary and secondary analyses

	t_0_ Baseline			t_1_ After 12-week exercise			t_2_ After surgery at hospital discharge			t_3_ 3 months after surgery			Between-group contrasts (change scores) 95% CI (*p*)
Mean, SD	Gp. 2	Gp. 4	Gp. 6	Gp. 2	Gp. 4	Gp. 6	Gp. 2	Gp. 4	Gp. 6	Gp. 2	Gp. 4	Gp. 6	
Isometric knee-extensor strength (Nm/kg)													Primary analysis Δ_t0-t1_ Secondary analysis Δ_t0- t2_, _t0-t3_
6-Minute Walking Test for distance (6MWT)													Secondary analysis Δ_t0-t1_, Δ_t0-t2_, Δ_t0-t3_
Stair Climb Test (SCT)													Secondary analysis Δ_t0-t1_, Δ_t0-t2_, Δ_t0-t3_
Knee Osteoarthritis Outcome Score (KOOS)							Na	Na	Na				Secondary analysis Δ_t0-t1_, Δ_t0-t3_
Oxford Knee Score (OKS)							Na	Na	Na				Secondary analysis Δ_t0-t1_, Δ_t0-t3_
Current knee pain (Numeric Rating Scale (NRS) 0–10)													Secondary analysis Δ_t0-t1_, Δ_t0-t2_, Δ_t0-t3_
Knee pain during the last week (NRS 0–10)							Na	Na	Na				Secondary analysis Δ_t0-t1_, Δ_t0-t3_
Need for surgery now (yes/don’t know/no)	Na	Na	Na				Na	Na	Na	Na	Na	Na	Secondary analysis
Exercise adherence													
• No. sessions (prescribed, completed, % completed)	Na	Na	Na							Na	Na	Na	Secondary analysis
• Seconds of total time-under-tension (TUT) (prescribed, completed, % completed)	Na	Na	Na							Na	Na	Na	Secondary analysis
Adverse events													Secondary analysis

The patients who choose not to be operated with TKA after the exercise period will be followed with annual outcome assessments as part of a small case study.

Descriptive statistics for the trial population will be presented as in Table 5.

**Table 5 Tab5:** Descriptive statistics

	Gp. 2	Gp. 4	Gp. 6	All patients
Age (years)				
Height (cm)				
Weight (kg)				
Gender (m/f)				
Index knee (r/l)				
Kellgren-Lawrence classification (I–IV)				

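### Table 3 row 10 states its hypothesis in percent adherence but gives the ANOVA outcome as counts and time-under-tension, and the protocol never says which is tested

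*Protocol article*

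**What the plan says.** All places are in the protocol article.

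- **Table 3, row 10, hypothesis:** "We hypothesize differences between groups in adherence (%) to the training intervention (i.e., higher number of sessions per week, the lower adherence" (in percent), with the order "Group 2 > Group 4 Group 4 > Group 6 Group 2 > Group 6".
- **Table 3, row 10, outcome measure:** the column meant to give unit and scale reads "Number of sessions, sets, repetitions and time-under-tension". The method is ANOVA, with Kruskal-Wallis if the data are not normal.
- **Secondary outcomes:** "exercise adherence (sessions, sets, reps, TUT", again without a percent.
- **Exercise adherence:** "patients are defined as adherent to the exercise intervention if > 75% of the prescribed exercise sessions are completed". The weekly thresholds given are 1.5, 3 and 4.5 sessions for groups 2, 4 and 6.
- **Table 4:** "No. sessions (prescribed, completed, % completed" and "Seconds of total time-under-tension (TUT) (prescribed, completed, % completed", both marked as secondary analysis in the between-group contrasts column. Sets and repetitions do not appear.
- **Table 6 (supplementary regressions):** exercise adherence is total time-under-tension (TUT) in seconds and the number of completed sessions, both as raw totals.

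**The concern.** Within one table row, the hypothesis and the variable meant to test it are on different scales. The other ANOVA rows for outcomes in Table 3 name the analysed quantity in that column (change in Nm/kg, change in metres walked). Read the same way, row 10 analyses counts and TUT.

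Counts are a sound measure of dose received, which is how Table 6 uses them after pooling the groups. They are not a measure of adherence when groups are compared, because the groups were assigned different amounts. A between-group test on counts mainly recovers the prescription.

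Adherence is recorded here so that poor uptake is not mistaken for an ineffective exercise. A comparison on the wrong scale could report a strongly significant group difference, with Group 6 on top, when patients in all groups had followed their prescription equally well.

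**Working it through.** **1. The plan's own figure.** Adherence threshold = 0.75 × prescribed sessions per week: 0.75 × 2 = 1.5, 0.75 × 4 = 3, 0.75 × 6 = 4.5. This matches the Exercise adherence section exactly, so that section treats adherence as a share of the prescription.

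**2. Full prescription.** Inputs from the Intervention section: 2, 4 or 6 sessions per week for 12 weeks, with 3 sets of 12 repetitions in every session.

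| | Group 2 | Group 4 | Group 6 |
|---|---|---|---|
| Sessions (12 × weekly) | 24 | 48 | 72 |
| Sets (× 3) | 72 | 144 | 216 |
| Repetitions (× 36) | 864 | 1728 | 2592 |

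Each row is 1:2:3. TUT has the same ratio whatever the seconds per session, because session content is identical across groups.

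**3. Equal adherence.** At 75% in every group the completed sessions are 18, 36 and 54. Suppose an SD of 25 percentage points (an assumption, since the protocol gives none) and 42 per group. The count SDs in groups 2 and 6 are then 0.25 × 24 = 6 and 0.25 × 72 = 18. The gap of 36 sessions has standard error √(6²/42 + 18²/42) = 2.93, so it is about 12 standard errors wide although adherence is identical.

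**4. Simulated rejection rates.** Each scenario used 4,000 trials with 42 per group, at the 5% level. All adherence levels and SDs are assumed.

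| Adherence in groups 2/4/6 | SD (points) | Rejects on counts | Rejects on percent |
|---|---|---|---|
| 75/75/75% | 25 | 100% | 5.7% |
| 80/80/80% | 20 | 100% | 4.5% |
| 80/80/80% | 30 | 100% | 4.4% |
| 90/80/70% | 20 | 100% | 98.9% |
| 90/80/70% | 30 | 100% | 76.9% |

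In the two 90/80/70% scenarios, where the hypothesis is true, the mean counts were ordered 2 < 4 < 6 in practically every trial.

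The Kruskal-Wallis fallback does not help, because the prescription separates the ranks as well.

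**5. When would counts follow the hypothesis?** Write adherence as a2, a4, a6.

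- Group 4's mean count is below Group 2's only if 48·a4 < 24·a2, that is a4/a2 < 1/2.
- Group 6's is below Group 4's only if 72·a6 < 48·a4, that is a6/a4 < 2/3.

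Both are needed for 2 > 4 > 6. Examples in sessions:

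- 90/75/60%: 21.6, 36.0, 43.2 (reverse of the hypothesis)
- 90/70/50%: 21.6, 33.6, 36.0 (still reversed)
- 90/60/40%: 21.6, 28.8, 28.8 (Groups 4 and 6 tie)
- 95/45/29%: 22.8, 21.6, 20.9 (agrees with the hypothesis)

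**6. Denominator for percent TUT.** Table 2 gives 1 min 36 s per set, and 3 × 96 s = 288 s = 4 min 48 s. The same entry states 4 min 42 s = 282 s per session. The gap is 6 s, and 6/288 = 2.1%.

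**The case against.** The strongest reply is that percent is what the authors mean. Row 10 is labelled as adherence to the intervention, and its hypothesis is expressly in percent. The outcome cell can be read as listing the dimensions on which adherence is measured, and it never says raw or total. The Exercise adherence section scales adherence to the prescription. Table 4 carries percent completed for sessions and TUT in rows that feed a between-group contrast. Raw counts also have their own use, as the dose variables in Table 6. A condensed article may leave the derivation of the variable to a fuller plan.

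Much of this stands. A reader might infer that the protocol has settled on testing raw counts. The documents do not support that, because percent may well be intended. Nor do they support the inference that the test must be significant whatever patients do, since steep enough falls in adherence would equalise or reverse the counts. It is also too much to say that a conclusion about the feasibility of the higher dosages would be wrong. The Discussion asks whether a single home-based exercise is feasible and draws no dosage-specific conclusion from this ANOVA.

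The reply does not remove the conflict. The outcome cell exists to give the unit and scale, and the scale it gives disagrees with the hypothesis beside it, so this is more than an omitted detail. The Secondary outcomes list and Table 6 use counts or totals under the name of adherence, which makes the literal reading a realistic one for an analyst. Table 4 offers percent for only two of the four measures, and beside it still lists the number completed.

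**Conclusion.** The point holds as an internal inconsistency: row 10's hypothesis is in percent, its listed outcome is in counts and TUT, and no passage says which form enters the ANOVA.

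If the row is followed literally, rejection is almost certain even with equal adherence. The group order then opposes the hypothesis unless adherence falls past one of the break-even ratios (1/2 for Group 4 against Group 2, 2/3 for Group 6 against Group 4). The 1:2:3 ratio and the break-even values follow from the protocol alone. The rejection rates rest on assumed adherence levels, SDs of 20 to 30 points and 42 patients per group.

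The reach is limited. Adherence is a secondary outcome in the Secondary outcomes section and Table 4, and sits under other outcomes in Table 3. The primary analysis and the sample size are untouched. It is worth correcting because the literal test would not address its own hypothesis.

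**What to change.** In Table 3 row 10, state that the analysed variable is, per patient over the 12-week period, completed/prescribed × 100 for each of sessions, sets, repetitions and TUT. Report the raw counts and total TUT descriptively. This agrees with the adherence definition and with Table 4, and extends the percent form to sets and repetitions. Fixing the 12-week window matters because patients who go on to surgery continue to be monitored until the operation, and the prescribed totals above do not cover that period.

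Before percent TUT is computed, reconcile the session TUT in Table 2 (4 min 42 s stated, 4 min 48 s from its own inputs), since that figure is the denominator.

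Comparing the share of patients above 75% between groups is optional.

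The cost is one table cell and one reconciled figure. No new data are needed, because the sensor already stores dates, sets, repetitions and TUT.

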#### Primary analysis

The primary analysis will be between-group contrasts for the primary outcome at the primary endpoint. Figure 6 illustrates a hypothetical presentation of changes in isometric knee-extensor strength at the primary endpoint for the three groups.

**Fig. 6 Fig6:**
[figure not shown]
A hypothetical presentation of group changes from baseline to the primary endpoint (after 12 weeks of exercise) for the primary outcome, knee-extensor strength

#### Secondary analyses

The secondary analyses will be between-group contrasts for the secondary outcomes at the primary and secondary endpoints. Figure 7 illustrates a hypothetical presentation of changes in isometric knee-extensor strength for the three groups during the whole trial period.

**Fig. 7 Fig7:**
[figure not shown]
A hypothetical presentation of group changes in knee-extensor strength over the whole trial period. NB, control data are from the academic literature [11] and so are the healthy, age-matched, control data (age 66.8 years (6.5 SD)) [7]

For all outcomes (primary and secondary), mean scores with corresponding standard deviations (SD), and between-group contrasts (change scores) with corresponding 95% confidence intervals (95% CI) and *p* value, will be reported at each endpoint (t_0_, t_1_, t_2_ and t_3_) for each group (groups 2, 4 and 6) (Table 4).

**Table 4 Tab4:** Outcomes for primary and secondary analyses

	t_0_ Baseline			t_1_ After 12-week exercise			t_2_ After surgery at hospital discharge			t_3_ 3 months after surgery			Between-group contrasts (change scores) 95% CI (*p*)
Mean, SD	Gp. 2	Gp. 4	Gp. 6	Gp. 2	Gp. 4	Gp. 6	Gp. 2	Gp. 4	Gp. 6	Gp. 2	Gp. 4	Gp. 6	
Isometric knee-extensor strength (Nm/kg)													Primary analysis Δ_t0-t1_ Secondary analysis Δ_t0- t2_, _t0-t3_
6-Minute Walking Test for distance (6MWT)													Secondary analysis Δ_t0-t1_, Δ_t0-t2_, Δ_t0-t3_
Stair Climb Test (SCT)													Secondary analysis Δ_t0-t1_, Δ_t0-t2_, Δ_t0-t3_
Knee Osteoarthritis Outcome Score (KOOS)							Na	Na	Na				Secondary analysis Δ_t0-t1_, Δ_t0-t3_
Oxford Knee Score (OKS)							Na	Na	Na				Secondary analysis Δ_t0-t1_, Δ_t0-t3_
Current knee pain (Numeric Rating Scale (NRS) 0–10)													Secondary analysis Δ_t0-t1_, Δ_t0-t2_, Δ_t0-t3_
Knee pain during the last week (NRS 0–10)							Na	Na	Na				Secondary analysis Δ_t0-t1_, Δ_t0-t3_
Need for surgery now (yes/don’t know/no)	Na	Na	Na				Na	Na	Na	Na	Na	Na	Secondary analysis
Exercise adherence													
• No. sessions (prescribed, completed, % completed)	Na	Na	Na							Na	Na	Na	Secondary analysis
• Seconds of total time-under-tension (TUT) (prescribed, completed, % completed)	Na	Na	Na							Na	Na	Na	Secondary analysis
Adverse events													Secondary analysis

The patients who choose not to be operated with TKA after the exercise period will be followed with annual outcome assessments as part of a small case study.

Descriptive statistics for the trial population will be presented as in Table 5.

**Table 5 Tab5:** Descriptive statistics

	Gp. 2	Gp. 4	Gp. 6	All patients
Age (years)				
Height (cm)				
Weight (kg)				
Gender (m/f)				
Index knee (r/l)				
Kellgren-Lawrence classification (I–IV)				

#### Supplementary analyses

The supplementary analyses will be simple regression models in which the three exercise dosage groups will be pooled, allowing us to utilize the full dataset; that is, the exercise dosage recorded by the sensors will be used in the analysis, not the prescribed exercise dosage. The dependent variables will be the change in primary and secondary outcomes from baseline to the primary endpoint and to the secondary endpoints. The independent variable will be exercise dosage, quantified in two ways: (1) as total TUT and (2) as number of completed exercise sessions for each patient (Table 6). Figure 8 illustrates a hypothetical simple regression model with the change in isometric knee-extensor strength (Nm/kg) at the primary endpoint and TUT.

**Table 6 Tab6:** Regression models for supplementary analysis

Supplementary analyses (primary outcome at primary endpoint)		
	Dependent variable (y)	Independent variable (x)
Linear regression model	Change in *isometric knee-extensor strength* Δ_t0-t1_	Exercise adherence Seconds of total time-under-tension (TUT) Number of completed exercise sessions
Supplementary analyses (secondary outcomes at primary and secondary endpoints)		
Linear regression models	Change in *isometric knee-extensor strength* Δ_t0-t2_, Δ_t0-t3_	Exercise adherence Seconds of total time-under-tension (TUT) Number of completed exercise sessions
	Change in *6-minute walk test for distance* (6MWT) Δ_t0-t1, t0-t2, t0-t3_	
	Change in *stair climb test* (SCT) Δ_t0-t1, t0-t2, t0-t3_	
	Change in *Knee Osteoarthritis Outcome Score* (KOOS) subscales Δ _t0-t1, t0-t3_	
	Change in *Oxford Knee Score* (OKS) Δ _t0-t1, t0-t3_	
	Change in *current knee pain* (Numeric Rating Scale, NRS) Δ _t0-t1, t0-t2, t0-t3_	
	Change in *knee pain during the last week* (Numeric Rating Scale, NRS) Δ _t0-t1, t0-t3_	
	Need for surgery (yes/don’t know/no)	
	Averse events

**Fig. 8 Fig8:**
[figure not shown]
A hypothetical simple regression model with the change in isometric knee-extensor strength (Nm/kg) at the primary endpoint and time-under-tension (TUT)

**Fig. 9 Fig9:**
[figure not shown]
Elastic exercise band fixation to an immoveable object (e.g., an elastic exercise band anchor behind a closed door) and placement around the ankle of the exercise leg

### Missing data

All analyses will follow the intention-to-treat (ITT) principle with a clear registration and reporting of the drop-out rate. All patients will be analyzed as randomized. To create a full analysis dataset for the intention-to-treat analyses, missing data will be imputed using multiple imputations.

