Patients with knee OA are characterized by decreased knee-extensor strength and this decrease in knee-extensor strength is associated with limitation of activities of daily living, independent of knee pain [7, 8]. Correspondingly, knee-extensor muscle weakness is found to be associated with increased risk of developing knee OA, progression of knee OA, symptoms of knee pain and decline in function [9, 10]. Clinically, patients diagnosed with end-stage knee OA who are awaiting TKA to reduce pain and disability are reported to have 35% reduced knee-extensor strength compared to healthy, age-matched persons [7]. Shortly after TKA, patients lose an additional 80% of their pre-operative knee-extensor strength [11]. This massive loss in knee-extensor strength severely limits functional performance and may delay hospital discharge in the large number of patients undergoing TKA every year [12]. One of the latest systematic reviews on the efficacy of exercise to reduce pain and disability in patients with knee OA showed that isolated knee-extensor strength exercise was more effective in reducing pain and disability if not combined with other forms of exercises (e.g., other muscle groups or cardiovascular training) [13]. In line with this, the 2014 international guidelines for non-surgical management of knee OA include strength exercise of the knee-extensor muscles [14].

Two recent randomized controlled trials have indicated that high-volume, pre-operative strength exercise may enhance pre- and post-operative knee-extensor strength as well as functional performance in patients undergoing TKA [15, 16]. Hence, there are indications that the applied pre-operative exercise dose seems related to pre- and post-operative efficacy, making a dose-response trial of pre-operative exercise particularly relevant.

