### Trial design

The trial is named the *QUADX-1 trial*. It uses a three-arm, parallel-group, randomized trial design with three intervention groups (exercise dosages) and no control group. No control group is included as the primary purpose of the trial is to investigate the dose-response relationship of the investigated knee-extensor strength exercise dosages. Based on the sample size estimation outlined below, 140 patients will be randomized (1:1:1) to one of three exercise dosages for 12 weeks. Outcomes will be assessed blinded at baseline before the start of the exercise (t_0_), after the exercise intervention, which is before possible surgery (t_1_, primary endpoint), at hospital discharge 1–8 days after surgery (if performed) (t_2_) and, finally, at 3 months after surgery (if performed) (t_3_). A flow chart of the trial is provided below (Fig. 1).

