## Discussion

In 2011, approximately 60,000 patients were registered in the Danish health care system with symptoms of knee OA and the annual incidence of knee OA has increased from 35.8 in 1997 to 155.2 in 2010 per 100,000 inhabitants [3]. Consequently, this population is very large and growing, which stresses the importance of optimizing the treatment offered to these patients. The *QUADX-1 trial* will add knowledge relating to which knee-extensor strength exercise dosage is most effective in increasing knee-extensor strength and whether a single, home-based (unsupervised) knee-extensor strength exercise is feasible in patients with end-stage knee OA.

The minimal treatment approach (single exercise) has been chosen as it is a pragmatic and time-saving solution [46]. Further, the rationale for investigating a home-based, single knee-extensor strength exercise is that it could improve exercise adherence as it is simple (minimal intellectual effort), does not take a long time (requires less surplus energy) and is likely to inflict less pain (less stress imposed on the knee joint). An exercise targeting the knee-extensor muscle is chosen as it is the single most important muscle for function in the knee OA population [9, 10, 13, 14].

In summary, the objective of the *QUADX-1 trial* is to investigate the efficacy of three different exercise dosages of pre-operative, home-based, knee-extensor strength exercise before and shortly after surgery in patients eligible for total knee replacement. The results will indicate which knee-extensor strength exercise dosage is most effective for increasing knee-extensor strength in the end-stage knee OA population. Furthermore, the results will indicate whether pre-operative knee-extensor strength exercise improves knee-extensor strength and function prior to surgery and whether this effect (if any) is sustained following surgery.

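### The ITT and imputation rule covers all analyses, but t2 and t3 exist only for operated patients, so those secondary comparisons either impute undefined values or are not ITT

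*Protocol article*

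**What the plan says.** The Missing data section sets three rules, none with an exception:

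- Scope: "All analyses will follow the intention-to-treat (ITT) principle with a clear registration and reporting of the drop-out rate".
- Population: "All patients will be analyzed as randomized".
- Imputation: "To create a full analysis dataset for the intention-to-treat analyses, missing data will be imputed using multiple imputations".

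The Trial design section makes the last two assessments conditional on an operation: "at hospital discharge 1–8 days after surgery (if performed) (t_2_) and, finally, at 3 months after surgery (if performed) (t_3". The Outcomes section repeats the condition. According to the Abstract and the Recruitment section, surgery is reconsidered at the orthopedic clinic after the 12 weeks of exercise, so some patients going without an operation is part of the design. For them the Secondary analyses section provides a different follow-up, as part of a small case study: "The patients who choose not to be operated with TKA after the exercise period will be followed with annual outcome assessments".

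Tables 3 and 4 plan between-group contrasts of change from baseline to t2 and t3, and Table 6 plans regressions on the same changes. None of them is limited to operated patients. Table 4 marks some cells as not applicable, but only where an item is not collected at a time point, not for patients without surgery. The Discussion says the results will show "whether this effect (if any) is sustained following surgery".

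**The concern.** An unoperated patient has no discharge value and no 3-month post-operative value. These values are undefined, not lost. A rule that fills every gap to complete the dataset would have to borrow them from operated patients.

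Three things are at stake:

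- **What is estimated.** The t2 and t3 contrasts would describe a hypothetical trial in which everyone was operated on, and the plan does not say so.
- **How the result is labelled.** If the gaps are left unfilled, the comparison covers a subgroup selected after randomization, possibly under the influence of dose. The ITT label would then be wrong.
- **The post-operative conclusion.** Strength shortly after surgery is part of the title and the stated purpose, yet the plan names no population for it.

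**Working it through.** **1. The passages side by side**

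| Question | Missing data section | Trial design, Outcomes, Secondary analyses |
|---|---|---|
| Which analyses? | All | Include contrasts at t2 and t3 |
| Which patients? | All, as randomized | t2 and t3 only after surgery |
| Gaps? | Imputed to a full dataset | No t2 or t3 visit is ever due without surgery |

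**2. The two possible readings**

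- *Literal.* All analyses, all patients and a full dataset mean that t2 and t3 values are imputed for unoperated patients. There is no true value to recover. The contrast is the one that would hold had everyone been operated on, and it is not declared.
- *Charitable.* Only visits that were due count as missing. Unoperated patients then drop out of t2 and t3, and the statement that all patients are analysed as randomized is false for those comparisons.

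The text needs correction under both readings.

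**3. The plan's own sample size**

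Inputs from the Sample size section: SD 0.22 Nm/kg, difference 0.15 Nm/kg, two-sided alpha 0.05, power 80%, 10% dropout. I used the noncentral F distribution for a three-group one-way ANOVA with evenly spaced means 0, 0.075 and 0.15:

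- Noncentrality at 42 per group = 42 × (0.075² + 0 + 0.075²) / 0.22² = 42 × 0.01125 / 0.0484 = 9.76.
- Power at 42 per group is 79.5%; 43 per group gives 80.5%.
- 126 / 0.9 = 140.

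The stated 126 and 140 are reproduced to within one patient per group. The point does not depend on them, but they give the base for step 4.

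**4. How many patients are affected**

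The documents do not give the share *s* of unoperated patients, so *s* is an assumption, shown over a range.

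- Patients with undefined t2 and t3 values = 140 × *s*.
- Share of t2 and t3 values imputed under the literal reading = 1 − (1 − *s*) × 0.9, using the plan's 10% dropout and assuming it falls equally on operated and unoperated patients.
- Operated patients per group = 126 × (1 − *s*) / 3, rounded down.
- Power is for a difference of 0.15 with SD 0.22, carrying the plan's t1 figures over to t2 and t3 (a further assumption).

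| Assumed *s* | Undefined, of 140 | Share imputed | Operated per group | Power, operated only |
|---|---|---|---|---|
| 10% | 14 | 19% | 37 | 74% |
| 30% | 42 | 37% | 29 | 62% |
| 50% | 70 | 55% | 21 | 47% |
| 70% | 98 | 73% | 12 | 28% |

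**5. Which covariates are safe at t2 and t3**

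I simulated two arms under assumed values: t1 change with SD 0.22 and a true difference of 0.15; 20% to 50% unoperated; odds of avoiding surgery rising with t1 change (log odds ratio 0.5 to 1.5 per SD); t2 change equal to t1 change minus 0.8 plus noise. Among operated patients, adjusting for t1 took the contrast from 0.108–0.145 to about 0.00. The model sends the whole dose effect through t1, so this follows by construction. It shows what t1 adjustment removes if later strength depends on dose through t1 strength.

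**The case against.** **Missing may mean due but not obtained.** The schedule makes t2 and t3 conditional, unoperated patients go to a separate follow-up, and the protocol nowhere says that their post-operative values will be imputed. This stands, so it cannot be stated as fact that such values will be imputed. It does not rescue the rule, because on this reading the ITT claim fails at t2 and t3.

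**A reader might infer that imputation biases the contrast.** The documents do not support that. In the simulation above, imputation from arm and t1 strength returned about 0.15, the true all-patients contrast, while the operated-only contrast was attenuated to 0.108–0.145. The objection to imputation concerns an undeclared target; bias has not been shown. The attenuation is a reason to label the operated-only comparison as unprotected by randomization.

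**A reader might set the surgical strength loss against the target difference.** The Background states: "Shortly after TKA, patients lose an additional 80% of their pre-operative knee-extensor strength". With a baseline near 1.0 Nm/kg, implied by the Sample size section's equating 0.15 Nm/kg with 15%, that is about 0.8 Nm/kg. But it is a within-patient loss expected in every arm, and a loss common to all arms cancels in a between-arm contrast. The statement also concerns the time shortly after surgery and says nothing about t3. It is no measure of the error here.

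**A reader might take Table 3 row 9 as expecting operation rates to differ by arm.** That row is the patient's own stated need for surgery at t1, not surgery performed. It makes dependence on dose plausible and no more.

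**Only secondary endpoints are touched.** This stands in full. The primary comparison at t1 precedes any operation.

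**Conclusion.** The concern holds as a moderate point, confined to the t2 and t3 secondary analyses. It is a rule stated too broadly, not a detail left to the statistical analysis plan: the article fixes ITT and full-dataset imputation for all analyses, and at t2 and t3 that is either an imputation of undefined values or a false ITT label. Its size depends on the unoperated share, which the documents do not give; each 10 percentage points adds 14 of the 140 patients. That surgery may depend on dose is plausible but not established. The t1 analysis needs no change on this account.

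**What to change.** In the Missing data section and Tables 3, 4 and 6:

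1. State that t2 and t3 outcomes are not applicable for patients who are not operated on and are not imputed for them.
2. At t2 and t3, limit multiple imputation to operated patients whose due visit was missed.
3. Label the t2 and t3 contrasts as conditional on surgery, not ITT and not protected by randomization.
4. Report the number operated in each arm beside these results.
5. Adjust these comparisons for baseline only. Do not adjust for t1: t1 strength is the primary outcome and the route by which dose would act on later strength.
6. In the Discussion, word the conclusion on a sustained effect for operated patients.

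This changes wording only and should be settled before the data are unblinded. The cost is fewer patients at t2 and t3, with the power loss shown above for the assumed shares, and results there that are non-confirmatory.
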